### 10.1.2 Reporting of serious adverse events (SAE) and other safety related events

Reporting of SAEs

All SAEs must be reported immediately and within a maximum of 24 hours to the Sponsor/Principle Investigator of the study. The Sponsor/Principle Investigator will receive an automatic message from the EDC system in case a SAE was entered into the eCRF at any study site. The Sponsor/Principle Investigator will re-evaluates the SAE within the eCRF and confirm or adapted the filled out SAE form.

Any SAEs resulting in death are reported to the lead Ethics Committee (by the Sponsor/Principle Investigator or his/her delegated person) within 7 days via BASEC and to Swissmedic.

SUSARs will be reported to the Ethics Committee (local event via local Investigator) via BASEC and to Swissmedic (via Sponsor/Principle Investigator) within 7 days, if the event is fatal, or within 15 days (all other events).

The Sponsor/Principle Investigator must inform all investigators participating in the clinical study of the occurrence of a SUSAR. All in the trial involved Ethics Committees will be informed about SUSARs in Switzerland via Sponsor/Principle Investigator via BASEC according to the same timelines.

Reporting of Safety Signals

All suspected new risks and relevant new aspects of known adverse reactions that require safety-related measures, i.e. so called safety signals, must be reported to the Sponsor/Principle Investigator within 24 hours. The Sponsor/Principle Investigator must report the safety signals within 7 days to the Ethics Committee (local event via local Investigator) via BASEC and to Swissmedic.

The Sponsor/Principle Investigator must immediately inform all participating investigators about all safety signals. The other in the trial involved Ethics Committees will be informed about safety signals in Switzerland via the Sponsor/Principle Investigator.

Reporting and Handling of Pregnancies

Not applicable

Periodic reporting of safety

SAE which did not result in death of the person as well as all occurred deaths will be summarised in an annual safety report that is submitted once a year to the local Ethics Committees and Swissmedic via the Sponsor/Principle Investigator.

### 10.1.3 Follow-up of (Serious) Adverse Events

During the study every step is taken to ensure, that all (S)AEs are identified and documented. Treating doctors and study centers are responsible to treat the (S)AEs and follow-up (S)AEs. At the routine follow-up at day 30 it is ensured, that all (S)AEs are identified and well treated. If a (S)AE occurs, all efforts will be undertaken to treat these (S)AEs (e.g. antiallergic treatment in case of an allergic reaction) and follow-up until it is resolved is ensured.

## Medical Device Category C studies

Not applicable.

## Medical Device Category A studies

Not applicable.

# STATISTICAL METHODS

## Hypothesis

The primary objective is to evaluate whether single-dose AP with TMP/SMX is non-inferior to 3-days AP with TMP/SMX (i.e. usual clinical care) regarding event rates of symptomatic UTIs. The non-inferiority margin δ is defined as the absolute difference in the event rates under intervention (p_sdAP_) compared to control (p_3dAP_).

H_0_: p_sdAP_ - p_3dAP_ ≥ δ

H_A_: p_sdAP_ - p_3dAP_ < δ

Non-inferiority will be declared if the upper limit of the two-sided 95% confidence interval of the absolute difference in event rates, p_sdAP_ - p_3dAP_, is smaller than the non-inferiority margin δ.

## Determination of Sample Size

Sample size was estimated to be able to able to show non-inferiority of single-dose AP compared to 3-day AP with at least 80 % power (1 – *β* = 0.8) at a significance level of *α* = 5 %, applying a 1:1 randomisation scheme. A drop-out rate of 10% was considered.

Determination of the non-inferiority margin $\delta$: There is no direct data available describing the effect of 3-day AP with TMP/SMX versus placebo on our primary endpoint. Based on internal data from the involved clinics, we assumed an expected UTI rate within 30 days under usual care (3-day AP) of 0.09 (9 %). A comprehensive meta-analysis (5) reported an overall risk ratio (RR) for symptomatic UTIs treated with AP versus placebo of 0.38. Applied to an expected UTI rate under 3-day AP of 9%, this corresponds to an expected (hypothetical) UTI rate under placebo of 23.68% (i.e. 0.2368 * 0.38 = 0.09) and an expected absolute treatment effect (absolute risk reduction, ARR) of 3-day AP versus placebo (M1) of 14.68% (ARR = 0.2368 – 0.09 = 0.1468). The non-inferiority margin was determined in order to preserve 70% of M1 (i.e. ARR*0.7; 10.28% on an absolute scale), which was judged a clinically important fraction. This would correspond to an absolute event rate under 1-day AP versus placebo of 13.4% (i.e. 0.2368 – 0.1028 = 0.134). Assuming an event rate of 0.09 (9 %) in both trial arms, this resulted in a non-inferiority margin $\delta$ = 4.4% (i.e. 13.4% - 9%).

In other words, when 100 patients undergoing TURP or GL would receive no treatment, 24 (i.e. 23.68%) would have a symptomatic UTI and 76 patients not. Would all these 100 be treated with 3 day AP, 9 (i.e. 9%) would still have a symptomatic UTI and 91 not. Would all these 100 be treated with a single AP (which still has 70% of the effect), approximately 13 patients would have a symptomatic UTI and 87 not.

We would consider it acceptable when approximately 4 more of 100 patients would have an UTI when bearing in mind that these 4 UTIs can be treated relatively straightforward with antibiotics and that simultaneously the use of AP can be strongly decreased in all 100 treated patients. This also very likely leads to fewer individual adverse events and resistant pathogens, and beyond this has important beneficial consequences for public heath due to lesser antibiotic resistance in general.

The sample size was calculated using a re-sampling procedure. Each sample size, n_i_=1,...,111 = 800, ..., 3000, was evaluated by simulating 999 individual samples of n_i_ patients based on the assumptions described above. The difference in the observed event rates p_idAP_ – p_3dAP_ was compared with the non-inferiority margin δ, using a two-sided 95 % confidence interval, calculated using a continuity-corrected modification of Wilson’s score method (41). Non-inferiority was declared if the upper limit of this 95 % confidence interval was no larger than the non-inferiority margin δ. Figure 2 shows the relationship between the total sample size (number of patients, not including drop-outs) and the expected absolute difference in the UTI rate between the two trial arms. For an assumed event rate of 9% in both trial arms, and a δ of 4.4%, a total of 1574 patients should be recruited, in order to have 1416 evaluable patients.

[figure not shown]
**Figure 2:** Total sample size needed to show possible non-inferiority of single-dose AP to 3-day AP, depending on the absolute difference in the UTI rate. An examples is shown for an absolute difference of 0% and a power of 80%. The curves are smoothed and for illustration only.

## Statistical criteria of termination of trial

Not applicable.

## Planned Analyses

### 11.4.1 Datasets to be analysed, analysis populations

Patients will be analysed according to the intention to treat (ITT) principle, i.e. all patients will be analysed according to the treatment group they were allocated to. Missing values will be handled as described in Section 11.5.

The per protocol (PP) analysis will include all patients without any major protocol deviation and for which the endpoint data is available (i.e. complete case analysis). Patients who miss more than one oral dose of study medication or who did not receive the intravenous TMP/SMX due to any reasons, will be classified as non-adherent to study drug and will be excluded from the per-protocol analysis.

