| Statistical Considerations: | Primary analysis  The difference in the proportion of UTIs between the single-dose AP and the 3-day AP arm will be compared with the non-inferiority margin using a two-sided 95 % confidence interval calculated according to the continuity-corrected modification of Wilson’s score method. The primary analysis will be based on the intention to treat (ITT) principle. We will also conduct a per protocol (PP) analysis. We expect a very low rate of non-adherence to the treatment regimens in both groups due to the nature of the intervention. Thus we do not expect substantial differences between ITT and PP analyses. We will base our interpretation on the ITT analysis under close consideration of the results of the PP analysis when reporting and communicating the results.  **Sensitivity analysis:** In order to evaluate the robustness of imputation method the ITT analysis of the primary analysis will be repeated using inverse probability censored weighting (IPCW) methodology.  **Subgroup analysis:** The difference in the UTI proportion between the study arms will be explorative assessed with 95% confidence interval for patients treated with TURP and patients treated with GL.  Secondary analyses  Analyses of all secondary outcomes will be exploratory in nature. All estimates will be presented with 95% confidence intervals. |
| GCP Statement: | This study will be conducted in compliance with the study protocol, the current version of the Declaration of Helsinki, the ICH-GCP or ISO EN 14155 (as far as applicable) as well as all national legal and regulatory requirements. |

study summary in local language

**Einzeldosis gegenüber einer Drei-Tage-Prophylaxe während einer transurethralen Resektion der Prostata oder Greenlight Laser Vaporisation der Prostata: eine pragmatische, multizentrische, placebokontrollierte Nichtunterleigenheitsstudie.**

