## Primary Outcome

Symptomatic UTI (based on clinical diagnosis) treated with antimicrobial agents (as per clinical judgement of the treating physician)

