## Criteria for withdrawal / discontinuation of participants

Enrolled patients have always the opportunity to withdraw from the trial without mentioning any specific reason at any time. In case of a SAE, the study drug will be stopped immediately and necessary treatment will be performed. In case of any complications, which require an antimicrobial therapy, the study drug will be stopped. Participations who stopped the study drug or withdrew consent will be asked if they are anyway willing to conduct the routine follow-up visit 30 days after surgery. Patients can state that they do not wish to be contacted for the study anymore and that also their physician shall not be contacted for outcome assessment.

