## Compliance with study intervention

The patients will independently take the study medications at day 0 (evening), day 1 and 2. In routine care, nurses regularly ask about the intake and enter this into the hospital information system. The study nurse will control the drug intake by confirming that the corresponding drug containers are empty 3 days after randomisation. To remain blinded the confirmation will be carried out by acoustically checking the drug container (shaking). In case that the drug containers were not emptied, the container will be sent to the Hospital Pharmacy of the University Hospital Basel, where the remaining tablets will be counted and destroyed.

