## Trial specific preventive measures

If an antibiotic has to be administered during the first 3 days after randomisation, the study medication needs to be stopped immediately.

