### 9.3.2 Allocation

Before the randomisation takes place, each patient will undergo a final eligibility check based on all at that time point available evidence from the laboratory and from asking the patient (i.e. evidence for UTI, cfu ≥10^5^/ml or antibiotic treatment in the last 7 days before surgery (i.e. randomisation)). If all questions can be answered with no (i.e. no evidence for (i) UTI; (ii) cfu ≥10^5^/ml; (iii) antibiotic treatment in the last 7 days before surgery (i.e. randomisation)), the patient will be randomised and will receive an identification code number via eCRF. The assessed parameters from the surgery are listed under Section 9.1. In the evening after the operation the patients will receive a drug container with the study medication (i.e. 5 tablets). They will be instructed to swallow one tablet on the evening of day 0 and the consecutive 4 tablets on day 1 and day 2 (always one after breakfast and one after dinner). Nurses will remind the patients about the intake of each tablet. Patients get and information sheet with the dosage instruction.

### 9.3.3 Day 1 and 2

Nurses will remind the patients about the intake of each tablet.

### 9.3.4 Day 3

At day 3, a urine culture (with antimicrobial resistance pattern) is performed. Furthermore, AEs of special interest as well as other potential AEs will be assessed. The study nurse will check if the entire study medication was taken as prescribed (See section 8.4)

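### The per-protocol rule removes patients whose early primary event forced the study drug to stop, so the set is partly selected on the outcome and is a weaker cross-check on the ITT result

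*Protocol*

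**What the plan says.** - **Exclusion (section 11.4.1).** The PP set contains patients with endpoint data and no major protocol deviation. Those left out as non-adherent are "Patients who miss more than one oral dose of study medication or who did not receive the intravenous TMP/SMX due to any reasons". No exception is made for a stop that the protocol itself requires.
- **Stopping (sections 7.4 and 8.6).** "In case of any complications, which require an antimicrobial therapy, the study drug will be stopped"; and "If an antibiotic has to be administered during the first 3 days after randomisation, the study medication needs to be stopped immediately".
- **Schedule (section 9.3.2).** The patient takes "one tablet on the evening of day 0 and the consecutive 4 tablets on day 1 and day 2", five in all.
- **Measuring adherence (section 8.4).** A container that is not empty at day 3 goes back to the pharmacy, where "the remaining tablets will be counted and destroyed".
- **Primary outcome (sections 5.1 and 9.2.1).** An event is a clinically diagnosed symptomatic UTI that was given antimicrobial treatment. Events during the hospital stay count.
- **Role of the PP analysis (synopsis, Statistical Considerations).** "We will base our interpretation on the ITT analysis under close consideration of the results of the PP analysis".

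**The concern.** Each rule is ordinary by itself. Together they make the primary outcome a cause of exclusion from the PP set. The event brings an antibiotic, the antibiotic stops the study drug, the stop leaves tablets in the container, and the tablet count makes the patient non-adherent. He did what the protocol asked and he had the outcome of interest.

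Section 11.4.2 warns that dilution can produce a false claim of non-inferiority under ITT, and the PP analysis is the only other look at the primary comparison that is meant to address adherence. The same section expects few non-adherent patients and small differences between the two analyses, so agreement will be read as reassurance. Part of that reassurance could come from deleting early failures. The arms differ only in the tablets on days 0 to 2, so early infections are one plausible place for harm from leaving the antibiotic out.

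**Working it through.** **1. Who is caught.** Tablets left, by time of the stop:

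| Stop occurs | Tablets left | In PP set? |
|---|---|---|
| before day 0 evening tablet | 5 | no |
| before day 1 morning tablet | 4 | no |
| before day 1 evening tablet | 3 | no |
| before day 2 morning tablet | 2 | no |
| before day 2 evening tablet | 1 | yes |

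The rule bites only on events treated before the day 2 morning tablet. Later events stay in the set.

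**2. Reproducing the plan's figure.** Inputs from section 11.2: 9% in both arms, margin 4.4 points, upper limit of the two-sided 95% continuity-corrected Wilson-based interval, 1416 evaluable patients (708 per arm). Calculated power is 80.2%, and 1416/0.9 gives 1574 to recruit. Both agree with the plan.

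**3. Effect of the removal.** Let p be the true event rate and f the share of events early enough to cause exclusion. These patients leave both numerator and denominator:

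PP rate = p(1 − f) / (1 − pf)

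Take true rates at the margin, 13.4% (single dose) and 9.0% (3-day), as in section 11.2. For f = 20% in both arms:

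- single dose: 0.134 × 0.8 / (1 − 0.0268) = 0.1072/0.9732 = 11.0%
- 3-day: 0.09 × 0.8 / (1 − 0.018) = 0.072/0.982 = 7.3%
- difference: 3.68 points instead of 4.40

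The margin stays at 4.4 points while the expected difference shrinks.

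**4. Results at 13.4% and 9.0%, 708 randomised per arm, no other exclusions.** The early share f is an assumption. The site data in section 3.1 pool in-hospital and day-30 events and do not give it.

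| f single dose | f 3-day | PP difference (points) | PP shows non-inferiority |
|---|---|---|---|
| 0% | 0% | 4.40 | 2.2% |
| 5% | 5% | 4.23 | 2.8% |
| 10% | 10% | 4.05 | 3.6% |
| 20% | 20% | 3.68 | 5.9% |
| 30% | 30% | 3.30 | 9.8% |
| 23% | 10% | 2.5 | 21% |
| 10% | 20% | 4.9 | 1.0% |

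The simulated percentages vary by about 0.1 point between runs. The 23% row puts half of the 4.4-point excess early, with 10% of the remaining events: (0.9 + 2.2)/13.4 = 23%. If none of the excess is early and f is 10% for the rest, the difference is 4.4 points, practically unchanged.

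**5. Equal true rates of 9%.** With f = 20% in both arms the PP rate falls to 7.3% in each, and the chance of passing the fixed margin rises from 80% to 86%.

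**6. Effect on the trial's conclusion.** ITT keeps every early event, so its false non-inferiority rate stays at 2.2% in every row. When both analyses are run on the same simulated trials, the chance that both pass is 1.9% to 2.2% in the scenarios where removal shrinks the difference.

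**The case against.** **The decision rests on ITT.** This stands. The PP analysis cannot create a claim that ITT has not already supported. A reader might infer from the table that the trial's own risk of a false claim rises to 10% or 20%. It does not: those are pass rates of the supportive analysis alone.

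**The window is short.** This also stands. It covers roughly the first 1.5 days. If events were spread evenly over 30 days, f would be about 1.5/30 = 5%. That removes about 708 × 0.134 × 0.05 = 4.7 single-dose patients and 708 × 0.09 × 0.05 = 3.2 3-day patients, and moves the PP error only from 2.2% to 2.8%. Both arms also receive the same intravenous dose on day 0. An extreme case can be built: if the whole excess and 20% of the common events are early, PP passes 78% of the time. That needs (4.4 + 1.8)/13.4 = 46% of single-dose events before the day 2 morning tablet, and nothing in the protocol supports such a share.

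**The protocol already warns about PP analyses.** Section 11.4.2 says that they rest on strong assumptions, and it commits to reporting both results and discussing differences. It names patient preferences and treatment switches. It does not say that the endpoint itself leads to exclusion, so the warning does not cover this case.

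**A required stop is not a missed dose.** That reading is possible, since the PP definition opens with major protocol deviations and the stop is compliance. But section 11.4.1 does not say so, section 8.4 counts leftover tablets whatever the cause, and the phrase on any reasons may govern both halves of the rule. The choice should not be left until the data are known.

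**Conclusion.** The point holds as a should-fix defect in the definition of the PP set. Sections 5.1, 7.4, 8.6, 9.3.2 and 11.4.1 together exclude every patient whose UTI is treated before the day 2 morning tablet, because of that event. The ITT primary analysis, its error rate and the sample size are not affected.

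The size cannot be fixed from the protocol. Over equal early shares of 5% to 30%, the chance that PP alone shows non-inferiority at the margin is 2.8% to 9.8%, against 2.2% without the removal. It is higher if the single-dose excess falls early.

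A reader might also infer that the bias always favours non-inferiority. That is the expected direction, because the arms differ only in the early tablets, but it is not certain. With early shares of 10% under single dose and 20% under 3-day prophylaxis, the PP difference widens to 4.9 points and the figure falls to 1.0%.

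**What to change.** Add to section 11.4.1, before unblinding: adherence is judged only up to a primary-outcome event; tablets not taken because study drug was stopped for that event or its antibiotic treatment do not count as missed; the patient stays in the PP set with the event counted. The rules in sections 7.4 and 8.6 on when study drug is stopped do not change.

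The cost is a short amendment and two data items: the reason for stopping study drug and the date the antibiotic was started. Tablet counts are already planned. A start date should not be assumed to be available: section 9.2.2 lists the compound, dose, frequency, duration and reason for each antibiotic, but no start date. After unblinding the same change would look data-driven.

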### 11.4.2 Primary Analysis

As primary analysis, the difference in the proportion in UTIs between the single-dose AP and the 3-day AP arm, will be compared with the non-inferiority margin using a two-sided 95% confidence interval calculated according to the continuity-corrected modification of Wilson’s score method (41).

Problems arising from misclassification of outcomes or from high attrition (missing data) that may “dilute” possible differences between groups are of special importance in non-inferiority trials. This may lead to falsely claiming non-inferiority in ITT analyses. However, per protocol analyses require strong assumptions and are prone to time-varying confounding (which may require careful adjustment for post-randomisation occurrences, for example treatment switches that would represent a protocol violation). However, post-randomisation confounding does not affect the causal interpretation of the ITT analyses. There is no consensus as to the choice of the primary analysis in non-inferiority trials (42).

This is a pragmatic trial aiming to inform the practical question about how to act, i.e. we aim to compare two treatment strategies. Therefore we will use the ITT analysis as our main analysis since it is the only method to estimate the unbiased causal effect of the intention to use the two treatment strategies (i.e. the intention to begin and adhere to a 1 vs 3 day AP). However, this has the risk that the different explanatory question about the causal effect of actually using the antibiotic treatment as specified in the protocol (i.e. under the -unrealistic- assumption of perfect adherence in all patients) will be more or less biased. This explanatory question, however, can only be evaluated in a per protocol analysis under strong and unrealistic assumptions (i.e. that all post-randomisation confounder leading to non-adherence are known, measured, and well understood so that they can be accurately modelled). Within the framework of this trial it is impossible to measure all possible post-randomisation confounders (e.g. patients’ preferences and values which may lead to non-adherence or treatment switch). Nevertheless, acknowledging these issues, we will use a PP analysis to estimate this per protocol effect. We assume that in this clinical situation only very few patients will be “non-adherent” due to the very short treatment period and that missing data is rarely (if ever) associated with the treatment allocation (i.e. missing completely at random) leading to small differences between the two estimates. In our publications (and other study reports), we will report the results of both analyses, discuss any differences and carefully describe the conceptual differences of both analyses

**Sensitivity analysis:** In order to evaluate the robustness of the imputation method the ITT analysis of the primary analysis will be repeated using inverse probability censored weighting (IPCW) methodology (details see Section 11.5).

**Subgroup analysis:** The difference in the UTI rate between the study arms will be estimated and reported with 95% confidence interval separately for patients treated with TURP and patients treated with GL. No other subgroups are pre-specified.

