## Methods of minimising bias

### 6.2.1 Randomisation

Patients will be randomly allocated to both groups in a 1:1 ratio. Randomisation will be performed via the electronic data capture (EDC) system, which is accessible via a standard browser on a WWW-connected device. The investigators will enter patient details into the electronic case report form (eCRF) via a secure web interface before randomisation takes place. In case of technical problems not allowing randomisation using the web-based randomisation system, local investigators will use the study treatment pack with the lowest number available in the centre and communicate the used study treatment pack to the trial management group. The used study treatment pack will then be assigned to the patient via the web-based eCRF.

The randomisation procedure will include a variance minimisation algorithm which will ensure that the study arms are balanced for some potential confounder variables, specifically centre and surgery type (TURP or GL). In order to avoid predictable alteration of treatment allocation, and thus potential loss of allocation concealment, patients will be allocated with a probability of 0.80 to each treatment group that would minimise the difference between the groups on the key prognostic factor.

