## Handling of missing data and drop-outs

Drop-outs will not be replaced. The number of drop-outs will be reported for each trial arm separately, indicating the reason for drop-out.

**Primary analysis:** For the ITT analysis, missing values will be imputed using multiple imputation methods. As sensitivity analysis, the analysis will be repeated using inverse probability censored weighting (IPCW) methodology (43). This approach accounts for missingness based on a logistic regression model for the probability of having a complete follow-up given past history covariates and outcomes. By using inverse weights, the impact of underrepresented subjects is inflated, so that one can observe associations that would have been observed if all subjects had stayed in the study, assuming the model is correctly specified. For the PP analysis, a complete case approach is applied where no missing values are possible.

**Secondary analyses:** Secondary analyses will be performed primarily as complete case analyses. For the key secondary endpoint [a] and secondary endpoints [r] and [s], additional (sensitivity) analyses will be performed, as described for the primary endpoint. For all other secondary endpoints, missing data will only be imputed or IPCW applied if the amount of missing values is considerable (i.e. more than 5% of values missing in one treatment group, more missing values than events in one group). This means that the number of patients may vary among analyses.

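### The primary interval uses neither centre nor surgery type, the two minimisation factors, and does not apply directly to multiply imputed data: a small, conservative loss that an adjusted risk difference would remove

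*Protocol*

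**What the plan says.** Section 6.2.1 describes minimisation with an allocation probability of 0.80, intended to ensure that "the study arms are balanced for some potential confounder variables, specifically centre and surgery type (TURP or GL").

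For the primary outcome, section 11.4.2 states that "the difference in the proportion in UTIs between the single-dose AP and the 3-day AP arm, will be compared with the non-inferiority margin using" the continuity-corrected Wilson method, with two-sided 95% limits. The synopsis says the same. Neither place names a stratum or covariate. Surgery type enters the primary outcome only as a subgroup.

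The decision rule is in section 11.1: "Non-inferiority will be declared if the upper limit of the two-sided 95% confidence interval of the absolute difference in event rates" lies below δ.

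Section 11.4.3 analyses secondary outcomes b–m, n–p and r–s with mixed models that contain study centre as a random effect. Surgery type is in none of them.

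Section 11.5 adds: "For the ITT analysis, missing values will be imputed using multiple imputation methods". An analysis by inverse probability of censoring weights serves as sensitivity analysis. How the interval is formed from several imputed data sets is not stated. Section 11.4.6 refers to a separate detailed analysis plan.

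**The concern.** There are two parts.

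First, balancing on factors that predict the outcome makes the arms more alike than simple randomisation would. A crude comparison does not credit this, so its standard error is somewhat too large. The protocol itself calls the two factors potential confounders and models centre for the exploratory outcomes, so leaving both out of the confirmatory comparison does not follow from its own design. What is at stake is power, in a design with almost none to spare.

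Second, the chosen interval takes one count and one sample size per arm. After multiple imputation the counts differ between data sets, and after weighting they are no longer counts. Someone must therefore choose how to build the interval that decides the trial, and that choice affects its width against the 4.4-point margin.

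**Working it through.** **Inputs.** From sections 11.1 and 11.2: a two-sided 95% interval, "with at least 80 % power", 1:1 allocation, and "For an assumed event rate of 9% in both trial arms, and a δ of 4.4%, a total of 1574 patients should be recruited", of whom 1416 evaluable (708 per arm) after 10% drop-out. From the pilot data in the background section: UTI in 13/156 (8.3%) with TURP and 9/87 (10.3%) with GL. Centre-specific rates are not given, so the ranges below are assumptions (five centres of equal size).

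**1. The plan's own figure.** Exact binomial enumeration of the probability that the upper limit falls below 0.044, 708 per arm:

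| Interval | Power (9% v 9%) | One-sided error (13.4% v 9%) |
| --- | --- | --- |
| Wilson, continuity-corrected (planned) | 80.2% | 2.18% |
| Wilson, uncorrected | 82.0% | 2.52% |

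The corrected interval reproduces 1416, and 1416/0.90 rounds up to 1574. Without the correction, 80% power is reached at about 1340–1360.

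**2. Size of the adjustment.** The ratio of the adjusted to the crude standard error is the square root of [mean within-stratum p(1−p)] / [overall p(1−p)].

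- Surgery type, pilot rates: √(0.082245/0.082338) = 0.9994.
- Centre rates 5, 7, 9, 11, 13% (assumed): √(0.0811/0.0819) = 0.995.
- Centre rates 3, 6, 9, 12, 15% (assumed): √(0.0801/0.0819) = 0.989.

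The crude standard error is thus about 0.1%, 0.5% and 1.1% too large.

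**3. In power.** Normal approximation: SE = √(2 × 0.09 × 0.91/708) = 0.01521, and power = Φ(0.044/SE − 1.96) = 82.5%. Multiplying the SE by 0.9994, 0.995 and 0.989 gives 82.5%, 82.8% and 83.3%. The gain is less than 0.1, about 0.4 and about 0.8 points.

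**4. Simulation of the minimisation** (probability 0.80, five centres, two surgery types, 3000 runs per scenario, Monte Carlo SE of the error rate about 0.3 points):

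| Centre rates | Power: crude corrected / crude uncorrected / stratified | Error: same order |
| --- | --- | --- |
| all 9% | 79.2 / 81.1 / 81.7% | 2.3 / 2.7 / 2.9% |
| 5–13% | 81.2 / 83.0 / 83.8% | 1.9 / 2.1 / 2.2% |
| 3–15% | 81.2 / 83.3 / 84.6% | 1.8 / 2.1 / 2.3% |

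Most of the step from the first to the third power figure comes from dropping the continuity correction. Part of the remainder arises because the stratified interval is of Wald type, which alone has exact power 82.6% against 82.0% for uncorrected Wilson. What is left for adjustment agrees with step 3.

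**5. Multiple imputation** (787 per arm, 10% missing completely at random).

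- A workable route: pool each arm's proportion by Rubin's rules, derive an effective sample size p(1−p)/T from the total variance T, and put it into the same corrected limits. With 20 imputations and 6000 runs, power was 80.7% and one-sided error 2.0%.
- A naive route: enter the averaged imputed proportions as if all 787 had been observed. The interval shrinks by √(708/787) = 0.948. Exact one-sided error is 2.8% with the correction and about 3.2% without it. With the correction it is 2.5% at 5% missing and 2.3% at 2% missing.

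**The case against.** The strongest defence is that nothing here endangers the conclusion. Ignoring balancing factors widens the interval, so the risk of falsely declaring non-inferiority does not rise. Surgery type, the only factor with data in the protocol, changes the standard error by well under one part in a thousand, and the pilot contrast is compatible with chance (Fisher p = 0.64). Any centre effect rests on assumed rates. All of this stands, and it sets the severity.

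Three stronger readings are tempting but not supported:

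- **That the interval cannot be pooled over imputations.** It can, by the effective-sample-size route in step 5. What the protocol lacks is a combining rule, and that may properly be left to the analysis plan, which is not at hand.
- **That the trial will run at an error of 2.8% or 3.2%.** Those figures belong to a naive procedure that the protocol does not prescribe, and the higher one also omits the planned correction. Even the naive route with the correction stays within 2.5% at 5% missing, and the protocol takes steps to limit missing outcomes (rescheduling up to day 35, a telephone call, hospital records).
- **That the continuity correction is a mistake.** The sample size was built on the same corrected interval and meets its target with it.

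The inconsistency remains: the confirmatory analysis ignores both allocation factors, while most exploratory models include one of them.

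**Conclusion.** The point holds as a minor one. The primary comparison is fixed without the two minimisation factors, so its standard error is slightly too large: about 0.1% for surgery type and 0.5–1.1% under the assumed centre spreads. The loss is about one power point or less and lies on the conservative side. The stated interval also does not apply directly to multiply imputed data. A valid construction exists, but a careless one would exceed the nominal 2.5%, reaching about 2.8% at 10% missing with the correction. The centre figures depend on assumed rates and equal centre sizes, and the imputation figures on 10% missing completely at random. Severity is low: an optional improvement.

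**What to change.** Make the primary estimate a risk difference adjusted for centre and surgery type, either stratified by Mantel-Haenszel or standardised from a logistic model. Combine the estimate and its standard error over imputations by Rubin's rules and compare the upper limit of the two-sided 95% interval with 4.4 points. Keep the crude continuity-corrected Wilson interval as a supportive analysis. This settles both parts at once, because the adjusted estimate comes with a standard error that can be pooled.

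The cost is a change of wording in section 11.4.2 and the synopsis, and slightly more programming. The sample size remains adequate. The one real concession is the small conservatism of the correction: one-sided error moves from about 2.2% towards the nominal 2.5% (2.2–2.9% for the stratified interval in the simulation, with a Monte Carlo SE of about 0.3 points). If the sponsor prefers to keep the crude interval as primary, the adjusted risk difference can instead be pre-specified as a sensitivity analysis, with the pooling rule for the crude interval written down.
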